**10 Roll-over protocol**

Patients randomized to and treated in arm 1, lopinavir/ritonavir + 2 NRTIs, can, in case of hyperlipidemia (grade 3-4) change treatment in a roll-over protocol.

Patients could be included in the roll-over protocol if:

1. treated with lopinavir/ritonavir + 2 NRTIs in arm 1, and

2. fasted total Cholesterol >1.6 x upper normal limit or fasted Triglycerides >7.50 g/L in two consecutive measurements

If the patient is eligible to the roll-over protocol, lopinavir/ritonavir (Kaletra®) is changed to atazanavir (Reyataz ®) 300 mg QD + ritonavir (Norvir®) 100 mg QD. The NRTI treatment should be continued.

Follow-up will be performed with the same on-trial evaluation schedule as if they had continued in the original study protocol.

In addition, blood lipids should be measured at the day of treatment change (-7 – 0 days) and also 4 weeks (3-5 weeks) after.

**11 Trial administration**

Simplified case report forms (CRF) will be provided for each subject by the co-ordinating centre. After completion of CRF, the investigator will send a copy of each page by e-mail to the co-ordinating centre after each visit. A copy will be printed and saved in patient records by the investigator at the study site. The data will be entered into a database at the co-ordinating centre.

**11.1 Trial monitoring**

In accordance with applicable regulations, a monitor (study nurse) will periodically contact the site, including conducting on-site visits. The extent, nature and frequency of on-site visits will be based on enrolment rate and quality of the documents provided by the site. During these contacts the monitor will check and assess the progress of the trial,, review trial data collected, conduct source document verification. This will be done in order to verify that the data are authentic, accurate and complete, that safety and rights of subjects are being protected and that the trial is conducted in accordance with the currently approved protocol, good clinical practice and regulatory requirements.

The contacts between the monitor and the sites will be recorded.

**12 Ethical considerations**

**11.1 Regulatory authority and ethics approval**

The study will be review and approved by the Ethics committee and Medical Products Agency (Läkemedelsverket) prior to initiating the study. In accordance with any applicable country-specific regulation, the responsible investigator will obtain approval from the appropriate regulatory agency prior to a site initiating the trial in that country.

The trial will be conducted in accordance with ICH-GCP and all applicable regulations, including, where applicable, the Declaration of Helsinki, June 1964, as modified by the 48th World Medical Association, republic of South Africa, October 1996.

**11.2 Subject informed consent**

The investigator or his/her designee will inform the subject of all aspects pertaining to the subject’s participation in the trial. The process for obtaining subject informed consent will be in accordance with all applicable regulatory requirements. The decision regarding subject participation in the trial that is made by the subject is entirely voluntary. The investigator or his/her designee must emphasise to the subject that consent regarding trial participation may be withdrawn at any time without penalty or loss of benefits to which the subject is otherwise entitled.

**11.3 Patient confidentiality**

The patient identity will only be known by the local sites. CRF’s and other records will be identified by a coded number only to maintain patient confidentiality. All computer entry and networking programs will be done with coded numbers only.

**13 Publications and authorship**

The findings from this trial are intended to be published in peer-reviewed journals. The site responsible investigators decide in agreement whether abstracts are to be submitted to conferences, and how the results are distributed if more than one manuscript is to be drafted.

The trial group as a whole will appear in an appendix in all published manuscripts. Co-authors are selected after a fair evaluation of primarily number of patients entered in to the trial and the level of involvement in the drafting of the manuscript and study protocol. Providing that several manuscripts are to be drafted, a fair rotation among the participating clinical sites of co-authorship slots will be done taking into consideration the number of patients enrolled.

Sponsors will have no influence on contents of the final manuscripts or abstracts.

**Table 1**

Clinical and laboratory evaluations at pre-entry and baseline

| **Evaluation** | **Screening&baseline** |  |
| --- | --- | --- |
|  | **d. -28 - 0** | **d. 0** |
| Informed consent | X |  |
| Entry criteria and demography | X | (X)f |
| Randomisation |  | Xi |
| CDC Classification | X | (X)f |
| Medicationsa | X | X |
| Adherence estimation |  |  |
| HIV-associated conditionsb | X | X |
| Plasma HIV-1 RNA quantitative PCRc | Xj | X |
| CD4 cell count | X |  |
| Blood lipids (Total Cholesterol, LDL, HDL, TG) (fasting) | X | (X)f |
| Hb, LPK, ASAT, ALAT, ALP, Bilirubin, S-amylas, Creatinin, fB-glukos | X | (X)f |
| Plasma ~~concentration of NNRTI and PI~~~~d~~  ~~and~~ 4bOHcd |  | X |
| Plasma sample collectione | X | X |
| Hepatits serology (HBsAg, anti-HCV)h | (X) |  |
| Weight | X | (X)f |

a Antiretroviral therapy including dose modifications, interruptions, discontinuations, and reasons for change should be indicated. All other drugs that are taken regularly should be indicated.

b At baseline, also the history of previous HIV-associated conditions.

c The HIV-1 RNA determination is done real-time at the site using routine virological methodology at that site, preferably the Roche Amplicor Ultrasensitive assay. The same method should be used for the individual subject throughout the trial.

d ~~12-24 hours after the last dose,~~ 10 ml heparin tube, centrifuged, plasma sent to Clin. Pharm., KU Huddinge (label: NORTHiv 4bOHc)

e 2 x 10 ml or 3 x 6 ml EDTA tubes, plasma collected and stored in –70oC at study site.

f if not performed on the previous visit

g ~~not necessary if HIV-1 RNA from screening visit performed within 2 weeks from baseline~~

h if not performed earlier

i randomisation could be performed before day 0 provided informed consent is signed and results from viral load and CD4 cell count are available

**j** HIV-1 RNA PCR obtained in clinical practice before initiation might be used for screening as long as it was obtained within the time limit (≤28 days before treatment initiation at baseline)

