**2.2 Inclusion**

HIV-1 infected patients naïve to antiretroviral drugs.

No limitations in CD4-cell counts or HIV-RNA levels.

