**5.4 Secondary endpoints**

1. Estimated adherence rate

2. Proportion of treatment discontinuations and changes due to different adverse events.

3. Decrease in HIV-1 RNA during the first 4 weeks of treatment (optional)

4. Proportion of patients with plasma HIV-1 RNA levels below 50 copies/ml after 4, 12, 24, 48, 72, 96, 120 and 144 weeks of treatment. Both Intention to Treat (ITT) and On Treatment (OT) analyses will be performed.

5. Changes in CD4+ T-cell count from baseline.

6. Time to discontinuation or changes of randomised treatment and reasons for this.

7. Incidence of adverse events.

8. Incidence of genotypic resistance to NRTIs, NNRTIs, and PIs that develops during the study

9. Proportion of patients with adjusted drug doses after therapeutic drug monitoring.

10. Correlations between plasma drug concentrations and virological outcome and adverse events.

11. Changes from baseline in plasma lipids.

12. Incidence of hypercholesterolemia and hypertriglyceridemia at baseline and follow-up.

13. Incidence of abnormal laboratory parameters (Hb, LPK, ASAT, ALAT, ALP, Bilirubin, S-amylas, Creatinin)

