***5.5.2 Virological failure***

Virological failure is defined as:

1. HIV-1 RNA >50 copies/ml in two consecutive measurements from week 24 and on, or

2. any rise in HIV-1 RNA >50 copies/ml in two consecutive measurements after viral load <50 copies/ml has been reached, or

3. HIV-1 RNA never <50 copies/ml after week 24, or

4. <1 log copies/ml drop in HIV-1 RNA from baseline to week 4 (provided HIV-1 RNA >50 copies/ml), or

5. <2 log copies/ml drop in HIV-1 RNA from baseline to week 12 (provided HIV-1 RNA >50 copies/ml)

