**7.1 Baseline characteristics and evaluations**

***7.1.1 Screening and baseline evaluation***

The site must obtain subject informed consent prior to the initiation of the study.

The pre-entry visit for screening must be conducted before, earliest 28 days prior to, the initiation of antiretroviral therapy.

The following evaluations should be performed at pre-entry (screening) visit:

 CD4-cell count

 Quantitative plasma viral load (HIV-1 RNA)

 Hepatitis serology (HBsAg and anti-HCV).

 Weight

CD4-cell count and quantitative HIV-1 RNA PCR obtained in clinical practice before initiation might be used for screening as long as it was obtained within the time limit (≤28 days before treatment initiation at baseline). Hepatitis serology results obtained earlier may be used instead.

The following evaluations should be performed at baseline (day 0):

 Entry criterias and demography including date of birth, gender, race, and mode of transmission of HIV

 CDC HIV classification 1993 version

 Previous HIV-associated conditions, i.e. B and C conditions according to the CDC HIV classification 1993.

 Weight (if not performed at screening)

 Blood lipids, i.e. total cholesterol, LDL, HDL, triglycerids (fasting)

 Hb, LPK, ASAT, ALAT, ALP, Bilirubin, S-amylas, Creatinin, fB-glukos

 Quantitative plasma viral load (HIV-1 RNA)

 2 x 10 ml plasma for storage in –70oC at study site.

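### A cheap gain in precision: the log-drop failure criteria are read from the day-0 HIV-1 RNA value alone, although a second pre-treatment value is already scheduled and could be averaged in

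*Protocol*

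**What the plan says.** - **Two scheduled values.** The HIV-1 RNA row of Table 1 reads "Plasma HIV-1 RNA quantitative PCRc | Xj | X", with one mark for screening (day -28 to 0) and one for day 0. Footnote g would have waived the second sample ("not necessary if HIV-1 RNA from screening visit performed within 2 weeks from baseline"), but it is struck through, so the current text asks for both.
- **Source and assay.** Footnote j allows a routine value at screening: "HIV-1 RNA PCR obtained in clinical practice before initiation might be used for screening as long as it was obtained within the time limit", which is 28 days before treatment. Footnote c says of the assay: "The same method should be used for the individual subject throughout the trial".
- **Meaning of baseline.** Section 7.1.1 opens its second list with "The following evaluations should be performed at baseline (day 0" and puts HIV-1 RNA on that list. Section 6.1 gives the screening value one stated use, stratification.
- **Where baseline matters.** Criterion 4 in section 5.5.2 is "<1 log copies/ml drop in HIV-1 RNA from baseline to week 4 (provided HIV-1 RNA >50 copies/ml". Criterion 5 is the same rule with 2 log at week 12. Neither names a confirmatory sample, whereas criteria 1 and 2 require two consecutive measurements. Virological failure is the first component of treatment failure (5.5.1), the primary endpoint.
- **Early decline.** Secondary endpoint 3 in section 5.4 is "Decrease in HIV-1 RNA during the first 4 weeks of treatment (optional". It names no reference value.
- **Entry.** Section 2.2 states "No limitations in CD4-cell counts or HIV-RNA levels".

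**The concern.** Criteria 4 and 5 each compare one pre-treatment value with one on-treatment value. Random error in either can move a patient whose true drop is near the threshold across it, in either direction. The analysis uses survival tests, so a false result at week 4 or 12 is an early event that stays in every later analysis. If error is alike in the arms, it dilutes a true difference.

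Part of this error is avoidable with samples the protocol already schedules. A common objection to averaging a screening value is that it was selected for being high or low. That is weak here, because entry sets no HIV-1 RNA limit.

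**Working it through.** **The plan's own figure.** Section 9 says that with 65 per group and a success probability of 0.70 in one group, the other must exceed 0.90 for 80% power (Fisher's exact test, two-tailed 0.05). Exact enumeration gives 77.5% at 0.90 and 80.3% at 0.905, so the statement is right.

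**Assumptions (none is in the protocol).** Within-patient SD of log10 HIV-1 RNA, assay plus biological: s = 0.15-0.30. Baseline mean 5.0 log10, SD 0.6. Mean true drop 1.8-2.2 log at week 4 and 2.6-3.0 at week 12, with SD components of 0.4-0.5. Between-patient SD of the early decline: 0.3-0.6.

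**Step 1: error variance of the observed drop.** With one baseline value it is s² + s² = 2s². With the mean of two it is s²/2 + s² = 1.5s². The ratio is 0.75: variance falls 25% and the SD falls 13% (√0.75 = 0.866).

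**Step 2: one patient with a true week-4 drop of 1.5 log.** The chance of a false result below 1 log is Φ(-0.5 / error SD).

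| s | Error SD, one value | Error SD, mean of two | False failure, one value | False failure, mean of two |
|---|---|---|---|---|
| 0.15 | 0.212 | 0.184 | 0.9% | 0.3% |
| 0.20 | 0.283 | 0.245 | 3.9% | 2.1% |
| 0.25 | 0.354 | 0.306 | 7.9% | 5.1% |
| 0.30 | 0.424 | 0.367 | 11.9% | 8.7% |

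At a true drop of 2.0 log the chance is below 1% either way.

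**Step 3: all patients, criteria 4 and 5 together, with the proviso of more than 50 copies/ml (simulation).**
- False failures fall from 2.0-10.7% to 1.6-9.2% of patients. The smallest gain is 1.97 - 1.61 = 0.36 points and the largest 8.92 - 7.38 = 1.54 points.
- Per 65 patients, the largest gain is 5.80 - 4.80 = 1.0 patient and the smallest 1.28 - 1.05 = 0.23.
- Missed true failures fall from 0.8-4.6% to 0.7-4.1%.
- Between 80% and 86% of the false failures remain (for example 4.82/6.03 and 9.22/10.67).

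**Step 4: each criterion alone.** Here s is 0.2-0.3, the mean drop is 1.8 (SD 0.4-0.5) at week 4 and 2.7 (SD 0.5) at week 12, and the assay floor is ignored. False failures fall from 3.6-7.4% to 2.8-6.1% at week 4 and from 5.2-8.8% to 4.3-7.3% at week 12. Even an error-free baseline would leave 56-64% of them, because the follow-up value carries its own error.

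**Step 5: primary-endpoint power.** If a share f of would-be successes in both arms is falsely failed, the success probabilities become 0.70(1-f) and 0.905(1-f). Fisher power with 65 per group then goes from 80.3% to 79.1% (f = 0.5%), 77.9% (1.0%) and 76.8% (1.5%). Removing that share is therefore worth 1.2, 2.3 and 3.5 points.

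**Step 6: early decline.** With between-patient SD d, the variance is d² + 2s² with one baseline value and d² + 1.5s² with two. For d = 0.6 and s = 0.15, 0.405 becomes 0.394 (-2.8%). For d = 0.3 and s = 0.30, 0.270 becomes 0.225 (-16.7%). In a comparison of two means, power of 80% becomes 81-87% if all 65 per arm contribute.

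**The case against.** The strongest reply is that nothing is wrong. The last value before treatment is a coherent reference for a drop from baseline, no passage contradicts it, and none forbids averaging. Handling of repeated baseline values is often left to an analysis plan. This stands, and it is why the point is an improvement and not an error. What remains is that the protocol itself fixes the failure definition and labels baseline as day 0, so the natural reading uses one of two available values.

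Four stronger readings are tempting, and the protocol does not support them:
- **Every patient has two values by the same method.** Table 1 is a schedule and footnote c says should. The screening value may come from routine practice, and the screening window runs up to day 0.
- **Early decline is measured from day 0.** Endpoint 3 names no reference, so this would be inference.
- **The single baseline materially weakens the primary analysis.** The 1-3.5 points are an upper bound. They ignore missed failures and patients who would fail later on another component, and the endpoint also counts discontinuation, switching and loss over 144 weeks.
- **Averaging cures the misclassification.** Most false failures remain, because the week-4 and week-12 values are single and no confirmation is named.

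The early-decline gain also assumes full participation. The extra early samples are optional, so fewer patients may contribute and power may be low with either reference.

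**Conclusion.** The point holds as a modest, nearly free gain in precision. The protocol schedules two pre-treatment HIV-1 RNA values, and criteria 4 and 5, read with section 7.1.1, use one. The 25% cut in error variance follows from arithmetic if the two errors are independent with equal SD and the true level is stable between samples. The rest depends on assumed SDs and mean drops: about 0.4-1.5 percentage points fewer false log-drop failures (roughly 0.2-1 patient per 65), slightly fewer missed failures, at most about 1-3.5 power points on the primary endpoint, and 3-17% less variance for the optional early-decline endpoint. A reader might infer that the sample-size statement in section 9 is wrong. It is not; it reproduces.

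**What to change.** In criteria 4 and 5 of section 5.5.2, define baseline HIV-1 RNA as the mean of the log10 screening and log10 day-0 values when both were measured by the same method, and as the day-0 value otherwise. State the same reference for endpoint 3 in section 5.4. Leave stratification on the screening value. Fix the rule before outcome data are examined: the trial is open label, and two candidate reference values exist.

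The cost is one sentence, with no new samples or visits. There are two small downsides. If the true level changes over the 28 days or less between samples, the mean lags by half of that change, alike in all arms because both samples precede treatment. Patients without a usable pair keep a less precise baseline than the others.

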**Table 2**

Clinical and laboratory evaluations at follow-up

| **Evaluation** | **Follow-up** |  |  |  |  |  |  |  |  |  |  |
| --- | --- | --- | --- | --- | --- | --- | --- | --- | --- | --- | --- |
|  | **d. 7**  **(6-8)**  **optional** | **d. 14**  **(12-16)**  **optional** | **d. 21**  **(19-23)**  **optional** | **w. 4**  **(3-5)** | **w.12**  **(10-14)** | **w.24**  **(22-26)** | **w.48**  **(45-51)** | **w.72**  **(69-75)** | **w.96**  **(93-99)** | **w.120**  **(117-123)** | **w.144**  **(141-147)** |
| CDC Classification |  |  |  | X | X | X | X | X | X | X | X |
| Medicationsa |  | X |  | X | X | X | X | X | X | X | X |
| Adherence estimation |  | X |  | X | X | X | X | X | X | X | X |
| Adverse events |  | X |  | X | X | X | X | X | X | X | X |
| HIV-associated conditionsb |  | X |  | X | X | X | X | X | X | X | X |
| Plasma HIV-1 RNA quantitative PCRc | X | X | X | X | X | X | X | X | X | X | X |
| CD4 cell count |  |  |  | X | X | X | X | X | X | X | X |
| Blood lipids (Total Cholesterol, LDL, HDL, TG) (fasting) |  |  |  | X | X | X | X | X | X | X | X |
| Hb, LPK, ASAT, ALAT, ALP, Bilirubin, S-amylas, Creatinin, fB-glukos |  | X |  | X | X | X | X | X | X | X | X |
| Plasma concentration of NNRTI and PId |  |  |  | X | (X)f |  | X |  | X |  | X |
| Plasma sample collectione | X | X | X | X | X | X | X | X | X | X | X |
| Weight |  |  |  | X |  |  | X |  | X |  | X |
|  |  |  |  |  |  |  |  |  |  |  |  |

a Antiretroviral therapy including dose modifications, interruptions, discontinuations, and reasons for change should be indicated. All other drugs that are taken regularly should be indicated.

b At baseline, also the history of previous HIV-associated conditions.

c The HIV-1 RNA determination is done real-time at the site using routine virological methodology at that site, preferably the Roche Amplicor Ultrasensitive assay. The same method should be used for the individual subject throughout the trial.

d 10-24 hours after the last dose, 10 ml heparin tube, centrifuged, plasma sent to Clin. Pharm., KU Huddinge

e 2 x 10 ml or 3 x 6 ml EDTA tubes, plasma collected and stored in –70oC at study site.

f if not performed on the previous visit

**Table 3**

Roll-over protocol

| **Evaluation** | **Extra visitsa** |  |
| --- | --- | --- |
|  | **d0**  **(-7-0)** | **w4**  **(3-5)** |
| Blood lipids (Total Cholesterol, LDL, HDL, TG) | X | X |
| Hb, LPK, ASAT, ALAT, ALP, Bilirubin, S-amylas, Creatinin, fB-glukos |  | X |
| Plasma concentration of atazanavirb |  | X |
| Plasma sample collectionc | X | X |
|  |  |  |
|  |  |  |

a The day when lopinavir/r is changed to atazanavir+r is regarded as d0 in the roll-over protocol. Besides the extra visits, the patient continues in the follow-up schedule as planned in table 2.

b 10-24 hours after the last dose, 10 ml heparin tube, centrifuged, plasma sent to Clin. Pharm., KU Huddinge

c 2 x 10 ml or 3 x 6 ml EDTA tubes, plasma collected and stored in –70oC at study site.

